### 6.7.4 Evaluation of technical criteria

- Implantation of fiducial markers : Yes / No
- Cumulative dosimetry : single/dual
- Boost session done : Yes / No
- Length of the boost session : Time elapsed between the patient entry and exit from the treatment room (bunker)

### 6.7.5 Evaluation of PSA kinetics during treatment

PSA will be obtained in the 48 hours following the last irradiation session of the first treatment phase will be compared to PSA before treatment, at the end of the treatment and then on a quarterly basis. PSA progression between these two samples will be correlated with the local control post-treatment.

### 6.7.6 Evaluation of sexual dysfunction

The International Index of Erectile Function is a questionnaire containing 15 questions, whose response is checked from 0 to 4 or 5 per question. It allows a semi-quantifiable evaluation of different aspects of masculine sexuality, grouped under the “areas” of erection, satisfaction, orgasm and desire. It was developed in the USA by [name] and has since been translated and validated in numerous languages, including French [Rosen 1997]. A simplified questionnaire containing only 5 questions, the IIEF 5, has been extracted for “screening” for erectile problems (appendix 11) [Rosen, 1999]. The complete version, meant for research and in particular the objective evaluation of treatment results, will be used in this study.

Interpretation will be a function of the number of points scored :

- 5 to 10 Severe erectile dysfunction

- 11 to 15 Moderate erectile dysfunction

- 16 to 20 Mild erectile dysfunction

- 21 to 25 Normal erectile function

- 1 to 4 Non interpretable

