| **ASSESSMENT CRITERIA** | Primary  Urinary or rectal toxicity: According to the NCI-CTCAE v3.0 rating scale (appendix 10). Acute toxicities are defined as all toxicities occurring in the 6 months following the start of radiotherapy. Late toxicities are defined as all toxicities occurring beyond 6 months.  **Secondary**   - Rate of local control at 3 years: non progression of : - PSA level according to the Phoenix definition (nadir to be obtained) - Clinical examination (rectal touch) - No pathological signal on MRI - Median time without progression for the entire cohort: interval between the date of inclusion and the date of progression, whether clinical (rectal touch) or radiological (prostatic MRI). - Median overall survival: Median time for the entire cohort comprising the time between the date of inclusion and the date of death, whatever the cause. - Survival without biological failure at 3 years: Phoenix criteria for PSA increase (nadir + 2 ng/ml) (see chapter 6.7.3) - Technical criteria: Implantation of markers, treatment time, cumulative dosimetry, administration and length of boost session - PSA kinetics during the entire treatment (between the two irradiation phases) and after treatment - Sexual dysfunction = international questionnaire IIEF 5 - Urinary discomfort = IPSS questionnaire |
| **STATISTICAL ANALYSIS** | The initial characteristics of included patients will be presented in the form of summary tables. Continuous variables will be summarized by conventional descriptive statistics parameters (median and outlying  values, mean and standard deviation when necessary). Category variables will be presented in the form of contingency tables (absolute frequency and percentage of each modality), additionally stating the number of missing data, along with the 95% confidence interval.  Subject inclusion and exclusion criteria will be checked against data entered into the case report forms when possible. Any deviations from the protocol will be documented.  Survival will be analyzed by the Kaplan-Meier nonparametric method. |

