## Appendix 11 : IIEF-5 questionnaire

| **In the Last 3 weeks...**  **How do you rate your confidence that you could get and keep an erection..?**  Very Low      Low      Moderate      High      Very High |
| --- |
| **When you had erections with sexual stimulation, how often were your erections hard enough for penetration..?**  Never/almost never   A few times   Sometimes (50:50)  Most times  Almost always/always |
| **During sexual intercourse, how often were you able to maintain your erection after you had penetrated (entered) your partner..?**  Never/almost never   A few times   Sometimes (50:50)  Most times  Almost always/always |
| **During sexual intercourse, how difficult was it to maintain your erection to completion of intercourse..?**  Extremely difficult    Very difficult    Difficult    Slightly difficult    Not difficult |
| **When you attempted sexual intercourse, how often was it satisfactory for you..?**  Never/almost never   A few times   Sometimes (50:50)  Most times  Almost always/always |

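### Section 6.7.6 names the complete 15-item IIEF, but the visits, the form and the score bands are for the IIEF-5, and the form as shown cannot yield the non-interpretable band

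*Protocol*

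**What the plan says.** Section 6.7.6 first introduces the long instrument: "The International Index of Erectile Function is a questionnaire containing 15 questions, whose response is checked from 0 to 4 or 5 per question". It then presents the short one as a screening extract: "A simplified questionnaire containing only 5 questions, the IIEF 5, has been extracted for" that purpose, with a pointer to Appendix 11. It closes the description with "The complete version, meant for research and in particular the objective evaluation of treatment results, will be used in this study".

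The interpretation bands follow directly. They run from "5 to 10 Severe erectile dysfunction", through moderate (11 to 15) and mild (16 to 20), to "21 to 25 Normal erectile function", with a separate line "1 to 4 Non interpretable".

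Elsewhere the instrument is the short form:

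- The synopsis, under assessment criteria, has "Sexual dysfunction = international questionnaire IIEF 5".
- Sections 6.6.1 (inclusion), 6.6.3 (3 months), 6.6.4 (6 to 30 months) and 6.6.5 (36 months) list the IIEF-5 and refer to Appendix 11. Section 6.6.6 (48 and 60 months) adopts the content of 6.6.4.
- The schedule in Appendix 2 has a row for the IIEF-5 and none for the complete IIEF.
- Appendix 11 prints five questions, the first being "How do you rate your confidence that you could get and keep an erection", each with five verbal options.

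**The concern.** Two things do not fit together. The sentence that fixes the instrument contradicts the rest of the protocol, and also the bands printed just below it. Separately, those bands include a non-interpretable category that the printed form, fully answered, does not appear able to produce.

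At stake is the secondary objective on sexual dysfunction caused by the strategy (section 5.2). Every patient receives the boost, so attributing dysfunction to treatment depends on comparing follow-up with baseline. If men without sexual activity are graded Severe, or lost as missing, at some visits, the reported distribution at those visits describes something other than erectile function. The instrument and its printed options also determine what is collected from inclusion onward. A later analysis document can choose a coding, but it cannot recover ten unasked items or an answer that was never offered.

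**Working it through.** **Inputs.** Long form: 15 items, each coded from 0 to 4 or 5 (section 6.7.6). Short form: 5 items with 5 options each (Appendix 11), no points printed. Bands: 1–4, 5–10, 11–15, 16–20, 21–25 (section 6.7.6).

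**Formula.** Lowest total = items × lowest code; highest total = items × highest code. Compare this range with the bands.

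**Reproducing the plan's graded range.** Five items coded 1 to 5 give 5 × 1 = 5 up to 5 × 5 = 25. That is exactly the range of the four graded bands.

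| Reading | Range of totals | Fit with the bands |
|---|---|---|
| 15 items, all coded 0–4 | 0 to 15 × 4 = 60 | 26–60 and 0 have no band |
| 15 items, all coded 0–5 | 0 to 15 × 5 = 75 | 26–75 and 0 have no band |
| Appendix 11, coded 1–5 | 5 to 25 | four graded bands reachable; 1–4 not reachable |
| Appendix 11, coded 0–4 | 0 to 5 × 4 = 20 | 21–25 not reachable; 0 has no band |
| Appendix 11 with a zero option added to items 2–5, item 1 coded 1–5 | 1 + 4 × 0 = 1 to 5 + 4 × 5 = 25 | all five bands covered, nothing outside |

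**Step 1, the instrument.** The two 15-item rows cannot be used with the bands of 6.7.6. If the sentence on the complete version were followed, every total above 25 would be unclassified. The bands therefore agree with the synopsis, visits, schedule and appendix, and the sentence is what is out of line.

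**Step 2, the form.** The natural reading of Appendix 11 is 1 to 5, because that matches the graded bands. Under it, the lowest total of a completed form is 5, so the 1–4 band stays empty. The last row shows what would fill it: a zero answer on items 2 to 5. Those items ask about erections with stimulation, about intercourse, or about attempts at it, so they presuppose activity; item 1 asks only about confidence. The zero option in that row is an assumption made for the check and does not appear in the document.

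**Step 3, incomplete forms.** If a man answers item 1 only and blanks count as nothing, his total is 1 to 5. Answers worth 1 to 4 would fall in the non-interpretable band, but the highest answer gives 5 and would be graded Severe. The protocol states no rule for totalling blanks, so this route to the 1–4 band is possible but not laid down.

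**The case against.** The strongest reply is that sites would hardly be in doubt. No 15-item form is supplied, and every collecting visit, the schedule and the appendix name the IIEF-5, so one sentence is wrong and nothing else. As a statement about likely conduct this is fair. The sentence still contradicts its own bands, and eight centres should not have to guess.

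On the form, a reader might infer that Appendix 11 cannot produce the score bands at all. The documents do not support that. Coded 1 to 5, it fills all four graded bands. The normal band becomes unreachable only under 0-to-4 coding, and the one coding statement in 6.7.6 that starts from 0 is about the 15-item version.

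A further reply is that text extraction may have dropped printed points or a zero option, since symbols are missing elsewhere in the protocol. This stands as a caution. The neighbouring IPSS form in Appendix 12 kept its codes and its lowest column, and all five items of Appendix 11 consistently show five options, but neither fact settles it. The form point therefore carries less weight than the instrument point and calls for checking the source page first. The instrument contradiction does not depend on the extraction.

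**Conclusion.** The contradiction over the instrument is certain: 6.7.6 names the 15-item IIEF, everything operational is the IIEF-5, and the bands suit only five items. The second part is narrower. On the form as shown, coded 1 to 5 and fully answered, only the 1–4 band cannot arise, and men without sexual activity have no matching answer and may be graded Severe or be missing.

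A reader might infer that sexual dysfunction will be mis-scored. That is not established: the item coding and the handling of blanks are not stated, so misclassification is a risk and not a demonstrated result.

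Nor can its size be stated. The protocol gives no proportion of sexually inactive men, and the median age of about 70 in section 4.1 is the French figure at diagnosis, not a trial figure. If 20–40% of men were assumed inactive at a visit, 20 to 40 percentage points would be the ceiling of wrongly graded Severe cases, reached only if every such man completed all items and scored 5 to 10; the floor is zero. A man graded Severe at both baseline and follow-up would add nothing to new dysfunction.

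This is a secondary, descriptive endpoint with no test or decision rule attached. The primary toxicity endpoint and the sample size of 76 are untouched. The correction is worth making because it is nearly free and affects what is collected.

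**What to change.** 1. In section 6.7.6, replace the sentence on the complete version by one stating that the IIEF-5 (Appendix 11) will be used. If the 15-item instrument is really wanted, supply that form and its own scoring instead, and change the synopsis, visits and schedule to match.
2. Print the item points, 1 to 5, on Appendix 11.
3. Check the source questionnaire page for a no-activity or no-attempt option scored zero. If it is absent, add it to the items that presuppose sexual activity.
4. State in 6.7.6 that totals of 1 to 4 arise through that option and are reported as not interpretable, separately from Severe.

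The cost is a sentence or two in 6.7.6 and one corrected questionnaire page. No visit, assessment or patient is added.

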## 5.2 Secondary objectives

- Evaluate local control at 3 years
- Determine the overall survival without metastatic disease
- Evaluate survival without biological failure at 3 years
- Evaluate technical criteria: implantation of fiducial markers, cumulative dosimetry, administration and length of boost session
- Study PSA kinetics during treatment (between the two irradiation phases) and after treatment
- Evaluate sexual dysfunction caused by this therapeutic strategy
- Evaluate urinary discomfort

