### 6.6.1 Inclusion examination

Patients eligible for the trial and having signed their consent to participate shall have an initial assessment within the 21 days preceding the treatment start.

 Clinical examination

- Weight, height, performance status or WHO (appendix 3)
- Digital rectal exam
- Cardiovascular risk factors (HBP, hypercholesterolemia, diabetes, stress)
- Prior medical and surgical history
- Disease history
- Tobacco use

 Blood tests

- CBC - Platelets

- Prothrombin rate, TCA, INR

- Urea, creatinine

- Tumor marker: PSA

 Paraclinic tests

- Tumor evaluation by pelvic spiral CT (could be the planning scanner) and pelvic and prostatic MRI
- Planning CT-Scan (1)
- Bone scan

 Questionnaires

- Sexual quality of life “IIEF-5” (appendix 11)

- Urinary difficulty “IPSS” (appendix 12) score >10 is an exclusion criteria

 Disease classification

- Gleason score, number of positive biopsies and total length of positive biopsies (appendix 5)

1. *For dosimetry, the planning scanner will be conducted with the most informative sequences identified by the diagnostic scanner and fused with the MRI.*

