### 6.7.7 Evaluation of urinary discomfort

The IPSS (*International Prostate Score Symptom)* is a self-administered questionnaire whose French version has been validated (appendix 12). The IPSS is made of 7 questions evaluating the severity of urinary symptoms. The questionnaire has been developed for the patient’s self-evaluation. Responses are checked from 0 to 5. Each question has six possible responses quantifying in increasing fashion the severity of symptoms. The total score can consequently be added, from 0 to 35 points (asymptomatic to very symptomatic). Patients can be classified as follows:

0-7: few symptoms

8-19: moderate symptoms

20-35: severe symptoms

##

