### 7.2.4 Identification of target volumes

CTV1 (first time of treatment) will include prostate and seminal vesicles.

- **Prostate** : The contour includes the entire gland. The definition of the apex is sometimes difficult : frontal and sagittal recontuctions (1 cm above the prostatic bulb) and image fusion with MRI. If doubt, especially if the apical biopsies are positive or if the lesion is situated low on the MRI, additional cuts will be added near the bottom. The principal anticipated toxicity of an irradiation administered too low is alteration of sexual function. The base is identified with the help of vesicular opacification
- **Seminal vesicles:** only the proximal part of the seminal vesicles will be included in the CTV1.

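### The IIEF is read on absolute score bands with no comparison to the inclusion score, so it cannot separate pre-existing erectile dysfunction from loss after treatment

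*Protocol*

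**What the plan says.** The sexual-function objective in Protocol section 5.2 is causal: "Evaluate sexual dysfunction caused by this therapeutic strategy". The urinary one is not: "Evaluate urinary discomfort".

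Section 6.7.6 gives one reading rule for the IIEF, in mandatory wording: "Interpretation will be a function of the number of points scored". The bands are 5–10 severe, 11–15 moderate, 16–20 mild and 21–25 normal, with 1–4 treated as not interpretable. The inclusion score is not mentioned.

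Section 6.7.7 describes the IPSS as a 0–35 total and adds "Patients can be classified as follows", with bands 0–7, 8–19 and 20–35.

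Both questionnaires are taken at inclusion, at 3 months and at the later visits up to 60 months (sections 6.6.1 and 6.6.3 to 6.6.6, Appendix 2). For the IPSS, section 6.6.1 adds "score >10 is an exclusion criteria". Sections 6.2 and 6.3 set no corresponding limit for the IIEF.

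**The concern.** A band at a single visit describes a man's state on that day. An objective about dysfunction due to treatment asks what changed. In a single-cohort trial the patient's own inclusion score is the only internal reference, and the section that says how the score is interpreted leaves it out.

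The protocol does name a pre-treatment comparison elsewhere: section 6.7.5 compares PSA with its value before treatment. The questionnaire sections do not.

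At stake is whether the IIEF result can be used at all as evidence of what the treatment does. A proportion in the moderate or severe band at 36 months mixes men who arrived that way with men who became so, in unknown shares.

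**Working it through.** **The plan's own figure.** The protocol gives no number for the IIEF or IPSS analysis beyond the band limits. Its sample size (section 6.8.3) reproduces with one-sided alpha 0.05, power 0.90, P0 = 0.85 and P1 = 0.95:

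n = [(1.645·√(0.85·0.15) + 1.282·√(0.95·0.05)) / 0.10]² = 75.1, rounded up to 76.

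The rule of at least 70 of 76 has exact alpha 0.0497 and power 0.914. Neither figure depends on the questionnaires.

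**IIEF, single patients (bands from section 6.7.6).**
- Inclusion 13, month 36 13: moderate, change 0.
- Inclusion 25, month 36 13: moderate, change −12.
- Inclusion 25, month 36 21: normal, change −4.
- Inclusion 21, month 36 20: mild, change −1.

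The first two men are read identically at 36 months. The last two show that band crossing alone is also a poor measure of change.

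**IIEF, cohort illustration.** Let b be the proportion below 21 at inclusion and l the proportion of men with normal function who later fall below 21. Both are assumptions; the protocol gives neither. Assume also that all 76 men have interpretable scores at both times and that no man recovers. Then:
- band prevalence of dysfunction at the visit = b + (1 − b)·l
- men with normal function at inclusion = 76·(1 − b)
- 95% half-width for l = 1.96·√(l(1 − l)/[76(1 − b)])

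| b | prevalence if l = 0 | prevalence if l = 0.20 | men at risk | half-width for l = 0.20 |
|---|---|---|---|---|
| 0.30 | 30% | 44% | 53 | ±10.7 points |
| 0.50 | 50% | 60% | 38 | ±12.7 points |
| 0.70 | 70% | 76% | 23 | ±16.4 points |

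The loss among men at risk is the same 20% in every row, while the band figure runs from 44% to 76%. Under these assumptions the band figure exceeds l whenever b is above zero and l is below 1, since b + (1 − b)l − l = b(1 − l).

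**IPSS (bands from section 6.7.7, baseline 0 to 10 by eligibility).** Largest worsening that leaves the band unchanged:
- from 0: 7 − 0 = 7
- from 7: 7 − 7 = 0
- from 8: 19 − 8 = 11
- from 9: 19 − 9 = 10
- from 10: 19 − 10 = 9

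A one-point rise from 7 to 8 changes band. Reaching the top band takes at least 20 − 10 = 10 points. The 11-point maximum occurs only at a baseline of exactly 8, the lower edge of "8-19: moderate symptoms".

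**The case against.** The strongest reply is that sections 6.7.6 and 6.7.7 are scoring keys within the assessment criteria and not analysis rules. The analysis section (6.8.2) says nothing specific about either questionnaire, and how repeated scores are summarised commonly sits in an SAP, which is not shown here. That stands as far as it goes: the absence of a change-score analysis would not by itself be a finding. But section 6.7.6 states how the score will be interpreted, and that interpretation does not match the objective it serves. An SAP could add paired change, but the protocol would still state a different reading.

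Three further replies stand and limit the point.
- **Harm is also measured against baseline elsewhere.** Section 6.7.1 defines an adverse event as a change from the patient's initial condition, and the CTCAE table in Appendix 10 grades erectile dysfunction as a decrease and urinary frequency as an increase over normal. The primary urinary toxicity is CTCAE-based.
- **The IPSS bands are permissive.** The 0–35 total is kept, the baseline is capped at 10, and the urinary objective has no causal wording.
- **Some supporting text is weak.** The remark in section 7.2.4, "The principal anticipated toxicity of an irradiation administered too low is alteration of sexual function", is about contouring. The median age of around 70 in section 4.1 is for French diagnoses in general, not for this cohort.

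A reader might go further and infer that baseline dysfunction will be reported as caused by treatment, that IPSS worsening will disappear, or that the two scales err in opposite directions. The documents support none of these. No section says the first. The second needs bands to be reported alone, which nothing requires. On the third, both scales can hide worsening within a band and both can count symptoms present at entry.

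**Conclusion.** The point holds for the IIEF. The stated reading cannot answer the stated objective, and the data for a better reading are already collected. The direction follows from the documents alone; the size depends on the proportion of men with dysfunction at inclusion, which the protocol does not give.

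The IPSS point is lesser and conditional: up to 11 points of worsening would go unseen only if the bands were the sole report.

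The scope is two secondary criteria. The CTCAE toxicity endpoint, the 76 patients and the 70/76 rule are untouched. It is worth correcting because the remedy is almost free.

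One inconsistency must be settled first. Section 6.7.6 says the complete 15-item questionnaire will be used, yet its 5–25 bands, Appendix 11 and the visit schedule all refer to the five-item form.

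**What to change.** - **Section 6.7.6, first step:** reconcile the statement that the complete version is used with the five-item bands and Appendix 11, before any band is applied.
- **Section 6.7.6, main reading:** report the paired change in IIEF score from inclusion with a 95% CI at each visit, including 36 months. A category-loss endpoint should not lead, because it counts 21 to 20 and misses 25 to 21.
- **Section 6.7.6, supporting figures:** add the proportion of men in the normal band (21–25) at inclusion who fall below 21, with its 95% CI. Men already near the bottom of the scale have little left to lose and dilute the mean change. Keep the bands as description, shown as transitions from inclusion to each visit.
- **Section 6.7.7:** report the paired change in total IPSS from inclusion with a 95% CI alongside the bands.
- **Section 5.2 and the synopsis:** replace *caused by* with *after*. Without a control group, even paired change includes ageing and other causes.

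The cost is wording and analysis only, with no new data or visits. The downside is that the figure among men with normal baseline function rests on fewer men: about 23 to 53 under the assumed range, with a 95% half-width of roughly 11 to 16 points if 20% lose function.
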